### Eligibility and allocation

Inclusion and exclusion criteria are summarised in the box 1.

Box 1Participant eligibility criteriaInclusion criteriaChildren must:be aged between 6 months and less than 12 years of agehave eczema diagnosed by an appropriately qualified healthcare professional (registered doctor, nurse or health visitor)mild eczema or worse (patient-orientated eczema measure score >2 within previous 28 days)The person giving consent must:have parental responsibility for the participantbe willing to use the randomly allocated emollient type as the only leave-on emollient for 16 weeks.Exclusion criteriaChild:known sensitivity to study emollients or their constituentsparticipating in another research study currently or in the last 4 monthsany other known adverse medical or social circumstance that would make invitation to the study inappropriate (as determined by GP surgery)The person giving consent:unable to give informed consentinsufficient written English to complete outcome measures

Participants will be randomised in a 1:1:1:1 ratio to the four groups, stratified by centre and minimised by baseline patient-orientated eczema measure (POEM — mild 3 to 7 vs moderate/severe 8+)^10^ and participant age (less than 2 years old vs 2 years and above) using a validated web-based randomisation system supplied by the Bristol Randomised Trials Collaboration. Allocation is secure, concealed and cannot be changed once made.

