### Statistical methods

The analysis and presentation of the trial data will be in accordance with Consolidated Standards of Reporting Trials guidelines.^23 24^ A full statistical analysis plan has been developed and approved by the independent statistician on the study’s trial steering committee ahead of analysis of post-randomisation data and will be made available via the study website.

Baseline characteristics of patients will be compared between the four arms by reporting summary statistics. Characteristics will be reported as means and SD, medians and IQRs or frequencies and proportions depending on the nature of the data and its distribution. If baseline characteristics of any two treatment groups differ by more than 10% or 0.5 SD then the effect of this variable on the primary outcome will be investigated in a sensitivity analysis.

Primary statistical analyses between the randomised groups will be conducted on an intention-to-treat basis. For the primary outcome we will use linear mixed models (weekly observations, level 1; nested within participants, level 2) to explore whether there are differences in mean POEM scores between treatment groups after adjusting for baseline scores and all stratification and minimisation variables used in the randomisation. Pairwise comparisons will be conducted to identify which intervention groups differed. To account for multiple testing, we will use a modified alpha of 0.0083 (0.05/6 pairwise comparisons equivalent).

Secondary outcomes will be analysed according to the data type and frequency of recording. Continuous outcomes measured at multiple time points will be analysed similarly to the primary outcome as described above. Continuous outcomes measured once after randomisation — such as EASI score — will be analysed using linear regression adjusting for baseline values where available. We will consider alternative methods should assumptions not be met.

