## Discussion

Factors that may influence patient preference for different types of emollient include disease severity, body site, cosmetic acceptability of the product, season/climate and packaging.^29^ Cultural factors may also influence choice and use.^30^ NICE recommends patients try different emollients in the clinic before choosing.^5^ This approach is not practical in primary care, and even in specialist settings the range of emollients available to try can be arbitrary — restricted by local formularies and influenced of pharmaceutical companies. Therefore, most patients consulting in primary care are unaware of differences between emollients; and many primary care clinicians will be unable to advise on grounds other than consistency or simple unit cost.

Some emollients are decades old and it has not been in the interest of manufacturers to submit their products in a head-to-head comparison with others in a clinical trial. In BEE, we are independently evaluating in a pragmatic trial, using a validated patient-reported primary outcome, the effectiveness of the four types of emollients commonly prescribed for children with eczema. In accordance with the recommendations of Harmonising Outcome Measures in Eczema, POEM and EASI will be used to measure patient-reported symptoms and clinical signs, respectively.^31^

Participants are unmasked, so knowing which emollient they’re using may bias assessment of emollient effectiveness. However, we have chosen a patient-reported outcome as the primary outcome because symptoms of eczema are more important to families of than objective measures which are based on skin appearance.^11^ We will minimise the potential for performance bias by ensuring that at the point of consent parents are willing to use any of the four emollients for the first 16 weeks. We will also measure at baseline parent opinion regarding the four different study emollients, and in a subgroup analysis explore whether reported effectiveness is linked to high/low prior expectations of effectiveness. The collection of an objective measure of eczema severity (EASI) by a masked researcher as a secondary outcome allows us to examine outcomes in relation to signs of eczema. Subject to additional funding, we plan to undertake a full economical evaluation to determine the cost-effectiveness of the four emollient types.

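### The stated model for EASI names only the baseline value and leaves out the randomisation factors that the primary model includes, so its standard errors would be slightly too large

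*Protocol article*

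**What the plan says.** The Eligibility and allocation section of the protocol article describes 1:1:1:1 randomisation "stratified by centre and minimised by baseline patient-orientated eczema measure" (3 to 7 versus 8 or more) and by age (under 2 years versus 2 years and above).

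The Statistical methods section then gives three adjustment rules for continuous outcomes:

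1. Primary outcome (weekly POEM): group differences are examined "after adjusting for baseline scores and all stratification and minimisation variables used in the randomisation".
2. Repeated secondary outcomes: "Continuous outcomes measured at multiple time points will be analysed similarly to the primary outcome as described above".
3. Outcomes measured once after randomisation, with EASI as the example: these "will be analysed using linear regression adjusting for baseline values where available".

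The same section says that a full statistical analysis plan has been approved. It is not among the documents reviewed.

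**The concern.** The second rule refers back to the primary model, so the randomisation factors carry over. The third does not refer back and names its own, shorter adjustment. An analyst working from that sentence would regress week-16 EASI on arm and baseline EASI and nothing else.

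When allocation is balanced on prognostic factors, the arms resemble each other more than chance alone would make them. A model without those factors counts the variation they explain as residual noise. The reported standard error then overstates the true uncertainty of the treatment comparison.

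This falls on an outcome that the trial has reason to protect. Parents and treating clinicians are unmasked, and the article accepts that their assessments may be biased. The Discussion points to "The collection of an objective measure of eczema severity (EASI) by a masked researcher as a secondary outcome" as a way of examining signs of eczema. If POEM and EASI lead to different conclusions, a difference in covariate sets is an avoidable complication.

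**Working it through.** **The plan's own figure.** The only sample size stated is for POEM: difference 3.0, SD 5.5, 90% power, alpha 0.05/6 (two-sided assumed, as the article does not say). With z = 2.638 for alpha and 1.282 for power, the sum is 3.920.

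- n per group = 2 × (3.920 × 5.5 / 3.0)² = 103.3, rounded up to 104
- four groups: 4 × 104 = 416
- with 20% loss: 416 / 0.8 = 520

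All three match the article. The point does not touch them. The article gives no SD, target difference or power for EASI.

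**Which outcomes the third rule reaches (Table 2).**

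- EASI: baseline and one follow-up visit at week 16. It falls under the third rule.
- DFI: after baseline at weeks 16 and 52. Repeated, so the second rule.
- ADQoL: after baseline at weeks 6, 16 and 52. Repeated, so the second rule.
- CHU-9D: after baseline at weeks 6 and 16. Repeated, so the second rule.
- Satisfaction with the emollient: week 16 only, with no baseline of its own. It falls under the third rule only if treated as continuous, which the article does not say.

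**Effect on the standard error.** Let R² be the share of the EASI variance left after baseline EASI that centre, age group and POEM category explain. The documents give no value, so 2 to 10% is assumed. Then SE with the factors / SE without = √(1 − R²), and the confidence interval without them is wider by 1/√(1 − R²) − 1.

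| R² (assumed) | SE ratio, with / without | Interval wider if omitted | Actual size of a nominal 5% test |
|---|---|---|---|
| 0.02 | 0.990 | 1.0% | 4.8% |
| 0.05 | 0.975 | 2.6% | 4.4% |
| 0.10 | 0.949 | 5.4% | 3.9% |

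The last column is 2 × [1 − Φ(1.96 / √(1 − R²))] and takes balance on the factors as perfect.

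**Effect on power.** Suppose, purely for illustration, that a pairwise EASI comparison has 90% power at alpha 0.05/6 with the factors in the model. Power without them lies between two limits:

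- no balance gained beyond chance: Φ(3.920 × √(1 − R²) − 2.638) = 89.3%, 88.1% and 86.0% at R² = 0.02, 0.05 and 0.10
- perfect balance: Φ(3.920 − 2.638 / √(1 − R²)) = 89.5%, 88.7% and 87.3%

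Minimisation should put the trial nearer the second limit.

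**Simulation.** This used 416 children, three centres, minimisation on POEM category and age within centre, 3000 runs and assumed effects. At R² of about 0.09, the type I error of a nominal 5% test was 3.6% without the factors and 4.3% with them. At R² of about 0.013 it was 4.3% and 4.5%. The Monte Carlo standard error of each rate is about √(0.05 × 0.95 / 3000) = 0.4 percentage points. The direction agrees with the formula, and the second gap is negligible.

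**The case against.** The strongest reply is that this reads too much into one clause of a condensed article. The sentence does not say that baseline is the sole covariate, nor that the randomisation factors are excluded. Covariate lists for secondary models are commonly left to the statistical analysis plan, and an approved one exists. That stands in part: the article does not prove that EASI will be analysed without these factors. What remains is that the article does not leave the matter open. It specifies an adjustment for this class of outcome, and that adjustment is shorter than the ones stated for the other two classes.

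The size can also be questioned. R² is assumed. Baseline EASI already measures severity, so a two-level POEM category may add little to it. This stands, and the gain may be at or below the low end of the range.

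A reader might infer four stronger points that the documents do not support:

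- **The EASI result would be biased or invalid.** Leaving balanced covariates out of a linear regression affects precision, not bias.
- **Centre matters because different assessors rate EASI at each site.** The article names three areas and describes masked researchers, but not how assessors map to centres. Stable rater differences would in any case be partly absorbed by baseline EASI.
- **Satisfaction would be analysed with no covariates, and the quality-of-life scales are affected too.** The Table 2 schedule does not bear this out.
- **EASI is the main safeguard against unmasked reporting.** The Discussion also relies on parents' willingness at consent to use any of the four emollients, and on a subgroup analysis by prior expectation.

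**Conclusion.** The point holds as a modest correction. On its wording, the article adjusts the masked EASI comparison for baseline EASI but not for centre, age group or POEM category, while the primary and repeated continuous outcomes adjust for all the randomisation factors. The treatment estimate is not biased. The reported standard error is too large by about 1 to 5%, and tests are slightly conservative, if the factors explain 2 to 10% of the variance left after baseline EASI. That range is an assumption with no source in the documents. The direction is secure; the size is not, and it is probably small. The conclusion depends on taking the sentence as the full specification, which the unseen statistical analysis plan could overturn.

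**What to change.** Reword the sentence so that continuous outcomes measured once after randomisation are analysed by linear regression adjusting for the outcome's baseline value where available and, in every case, for centre, age group and baseline POEM, as in the primary model. If the statistical analysis plan already specifies this, only the article's sentence needs to be brought into line with it.

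The cost is one clause and a few degrees of freedom: two for three centres, one for age group and one for POEM category, so four in a model with about 416 children (the POEM figure, borrowed because none is given for EASI). Data collection, sample size and the primary analysis stay as they are.

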### Nested qualitative study

The aims of the qualitative study are first, to support and optimise participant recruitment and retention; and second, to complement, explain and aid understanding of the quantitative findings

#### Baseline appointment recordings

To meet the first aim, a sample of baseline appointments (at least one per recruiting researcher) will be audio-recorded and reviewed by a qualitative researcher. Using a structured template, the interaction will be reviewed to ensure key information is relayed and parent understanding checked. Recommendations will be feedback individually to the relevant researcher and collectively (anonymised) to other recruiting researchers and the trial management group. Prior to the start of the baseline appointment, parents will be asked to give verbal consent for the recording, with written consent obtained at the end of the appointment.

#### Interviews with parents and trial participants

To meet the second aim, we will interview parents and, at their discretion, the participating children themselves, at 4 weeks and 16 weeks after randomisation. The design is cross-sectional, with different families interviewed at each time point. However, where particularly interesting issues emerge, we may speak to a family at both time points. Parents will indicate on the trial consent form whether they are willing to be approached for these.

The 4 week interviews will focus on the initial use and acceptability of the assigned emollient. We will conduct up to five interviews in each trial group (total ~20), purposively sampling by: recruitment centre, age of child, eczema severity and allocated type of emollient. We will include those who have stopped using the allocated treatment or switched emollient.

The 16 week interviews will focus on the overall experience of using the assigned emollient, perceived effectiveness, planned future use of emollients and experience of taking part in the trial. The sampling criteria will be the same as for the 4 week interviews, with the additional criterion of intentions regarding future emollient use. We expect to achieve data saturation by conducting up to 10 interviews in each trial group (total ~40).

Interviews are expected to last between 30 to 60 min. Topic guides (including subtopic guide for children) will be used but with flexibility to allow unanticipated issues to emerge and be further explored in later interviews. Interviews will be captured using an encrypted digital voice recorder, transcribed and anonymised to protect confidentiality.

The interview data will be analysed thematically, using a combination of deductive and inductive coding^25^ and adapted techniques of constant comparison.^26^ Analysis will be led by the qualitative researcher, with input from the qualitative co-applicants and trial management group. Data management and coding will be aided by use of NVivo software. Data will be compared within and across trial group, with attention to converging and diverging perspectives. The themes will be written up as interpretive summaries with illustrative verbatim quotes that represent the range of expressed views.

### Monitoring, safety and audit

As the randomised treatments within this study do not differ from common usual clinical practice, risk-based monitoring will be implemented in line with a risk-assessment. Data on adverse events will be collected by parent self-report. No interim analyses are planned.

An independent Data Monitoring Committee has been established and terms of reference have been drawn up and agreed. The committee will meet at least annually, and its role is to safeguard the interests of the trial’s participants, potential participants, investigators and sponsor; to assess the safety and efficacy of the trial’s interventions, and to monitor the trial’s overall conduct, and protect its validity and credibility.

The sponsor organisation is the University of Bristol. Adverse event reporting will be in accordance with local procedures.

The trial may be prematurely discontinued due to lack of recruitment or by the sponsor, chief investigator, regulatory authority or funder based on new safety information or for other reasons given by the trial steering committee or data monitoring committee, regulatory authority or ethics committee concerned.

### Public and patient involvement

In 2013, the James Lind Alliance published the eczema research priorities for patients and healthcare professionals and ‘Which emollients are the most effective and safe in treating eczema?’ emerged as one of the highest ranked uncertainties.^27^

Co-author AR is mother of children with eczema and a member of Nottingham Support Group for Carers of Children with Eczema. We have established a group of parents of children with eczema, who helped develop the study and want to support our ongoing work through meetings and email communication. A patient and public involvement (PPI) member sits on the trial steering committee. We will use the internet and social media to promote wider patient engagement.

PPI has helped us to frame the research question around, ‘Which emollient to prescribe first?’ for childhood eczema, acknowledging that individuals differ in their experiences of effectiveness and tolerability of different emollients. It has also gave us a clear steer that including a non-emollient group would be unacceptable to many families, favoured POEM as the primary outcome and highlighted how emollient use may be a ‘trade off’ between effectiveness and acceptability.

Ongoing PPI involvement has informed both qualitative and quantitative data collection and helps ensure that the study continues to focus on delivering clinically important outcomes that are meaningful to patients.^28^

## Ethics and dissemination

## Protocol amendments

Any amendments to the protocol will be reported accordingly to the regulatory bodies, with a copy of the current protocol (V.6.0 currently) available for download from the study website. Amendments to date are listed in online supplementary appendix 1.

10.1136/bmjopen-2019-033387.supp1Supplementary data

### Consent and assent

Written consent for taking part in the trial will be received by a researcher from the parent or guardian of the participant at their baseline appointment. For children approximately 7 years and older, the option of providing assent will be offered alongside parental consent (see online supplementary appendix 2).

10.1136/bmjopen-2019-033387.supp2Supplementary data

### Confidentiality and access to data

The database and randomisation system will protect patient information in line with the data protection legislation. Trial staff will ensure that participants’ anonymity is maintained through protective and secure handling and storage of patient information at the lead centre. The chief investigator will have access to and act as custodian of the full data set.

### Ancillary and post-trial care

After the 16 week primary outcome period, participants will be free to change their emollient if they wish. Conversely, they will be able to continue with their allocated emollient after they have completed follow-up.

### Dissemination and data sharing

A series of stakeholder meetings will raise study awareness among and share progress and findings with policymakers, voluntary groups, clinicians, patients, families. Study progress, outputs and a summary of findings will be made available via a study website and Twitter account; and summaries distributed to participating families and GP surgeries. Findings will be submitted for presentation at conferences and written up for publication in a peer-reviewed journal(s), which may include integration of the quantitative and qualitative findings. The International Committee of Medical Journal Editors has criteria for authorship will be observed and no professional writers will be employed.

No later than 3 years after the completion of the study, we will deposit a de-identified data set in an appropriate data archive.

## Discussion

Factors that may influence patient preference for different types of emollient include disease severity, body site, cosmetic acceptability of the product, season/climate and packaging.^29^ Cultural factors may also influence choice and use.^30^ NICE recommends patients try different emollients in the clinic before choosing.^5^ This approach is not practical in primary care, and even in specialist settings the range of emollients available to try can be arbitrary — restricted by local formularies and influenced of pharmaceutical companies. Therefore, most patients consulting in primary care are unaware of differences between emollients; and many primary care clinicians will be unable to advise on grounds other than consistency or simple unit cost.

Some emollients are decades old and it has not been in the interest of manufacturers to submit their products in a head-to-head comparison with others in a clinical trial. In BEE, we are independently evaluating in a pragmatic trial, using a validated patient-reported primary outcome, the effectiveness of the four types of emollients commonly prescribed for children with eczema. In accordance with the recommendations of Harmonising Outcome Measures in Eczema, POEM and EASI will be used to measure patient-reported symptoms and clinical signs, respectively.^31^

Participants are unmasked, so knowing which emollient they’re using may bias assessment of emollient effectiveness. However, we have chosen a patient-reported outcome as the primary outcome because symptoms of eczema are more important to families of than objective measures which are based on skin appearance.^11^ We will minimise the potential for performance bias by ensuring that at the point of consent parents are willing to use any of the four emollients for the first 16 weeks. We will also measure at baseline parent opinion regarding the four different study emollients, and in a subgroup analysis explore whether reported effectiveness is linked to high/low prior expectations of effectiveness. The collection of an objective measure of eczema severity (EASI) by a masked researcher as a secondary outcome allows us to examine outcomes in relation to signs of eczema. Subject to additional funding, we plan to undertake a full economical evaluation to determine the cost-effectiveness of the four emollient types.

Recruitment started in January 2018 and follow-up of the last participant is scheduled by February 2021. Findings from the BEE study, comparing the clinical effectiveness and acceptability of commonly used different emollients, will provide evidence on which clinicians and carers/patients can decide which emollient to try first. Our aim is not to reduce choice, but to reduce uncertainty and the consequences of ‘trial and error’ prescribing. Smarter prescribing will help prescribers and carers gain ‘control’ over the eczema more quickly, reduce frustration and inconvenience for families and potentially produce cost savings to the NHS through cost-effective prescribing and fewer repeat consultations to change emollients.
